## 1.0 THE NEED FOR A TRIAL

### 1.1 Problem to be addressed.

To date, the Coronavirus Disease 2019 (COVID-19) pandemic, caused by severe acute respiratory syndrome coronavirus 2 (SARS-CoV-2), has resulted in over 36 million documented cases and over 1 million deaths. Patients infected with SARS-CoV-2 experience unusually high rates of critical illness requiring advanced airway management and intensive care unit admission. Data from the epicenter of the COVID-19 outbreak in Wuhan, China, indicate that 2.3 to 3.2% of patients with COVID-19 required endotracheal intubation (ETI) and invasive ventilation at some point during their illness. The overwhelming scale of the pandemic and severity of disease presents a serious threat to the health of frontline workers. In Italy, 9% of over 22,000 SARS-CoV-2 cases were healthcare providers (HCP). Aerosol-generating medical procedures (AGMPs), such as bag-valve-mask (BVM) ventilation, laryngeal mask airway insertion (LMA), and ETI are commonly required for critically ill COVID-19 patients. AGMPs produce airborne particles, contributing to the disproportionately high risk of infection amongst HCPs working in acute care areas. Strategies to mitigate HCPs exposure to and infection from COVID-19 during AGMPs are required to maintain the integrity of the healthcare workforce during the pandemic.

To minimize HCP exposure during high-risk AGMPs, an aerosol box has been developed to place over the head of the patient, shielding the provider's face from aerosols. This invention, and various different adaptations, have been implemented by hospitals around the world for airway management in COVID-19 patients. During the COVID-19 pandemic, members of our research team have developed and utilized an adapted version of the aerosol box for the management of COVID-19 patients undergoing AGMPs (Figure 1). Little is known about the effectiveness of the aerosol box during BVM ventilation, LMA insertion or ETI. Several small studies done in simulated environments with manikin heads enclosed by aerosol boxes demonstrate variable containment of particles aerosolized by a simulated cough, but none of these studies incorporated wall suction as a means to provide negative airflow. A more recent study demonstrated significantly reduced levels of airborne particles measured at the laryngoscopist's head when using an aerosol box with wall suction, compared to an aerosol box without wall suction. Despite this promising data, there has been concern about the impact of aerosol box use on procedural performance, which may potentially have a negative effect on patient outcomes. Amongst a group of 12 anesthesiologists, aerosol box use was associated with longer intubation times and lower first-pass success rates when attempting intubation on an adult manikin head. The main limitations of this study were that participants received only very brief training, and did not have an airway assistant to support them during ETI. To date, there have been no single or multicenter studies assessing the use of an aerosol box with trained airway teams (i.e. airway provider and airway assistant). Studies have focused primarily on the task of intubation, without any evidence describing the impact on performance of LMA insertion or BVM ventilation. Furthermore, no studies have quantified the degree of contamination resulting from AGMPs with and/or without the use of an aerosol box while concurrently measuring clinically important performance outcomes (eg. time to intubation or LMA insertion).

Our study will provide evidence to: (a) determine if aerosol boxes are effective in reducing provider and environmental contamination during performance of AGMPs by a trained airway team; (b) evaluate if using an aerosol box adversely affects time to completion and first pass success rates for ETI and LMA insertion; and (c) describe the patterns of contamination after commonly performed AGMPs. Our *long-term goal* is to provide empiric evidence to enhance HCP safety during AGMPs while delivering high quality care. This will be accomplished by creating clinical scenarios within a simulated clinical environment, as conducting a similar study on real COVID-19 patients would be fraught with challenges and risks. By using manikins as surrogate patients, we will quantitatively measure HCP and environmental contamination after performing AGMPs. Measuring time to achieve

successful ETI and LMA insertion and first-pass success rates provide clinically relevant parameters that can be balanced against the degree of HCP contamination to inform clinical practice and potential changes to institutional policy.

**Figure 1 – Aerosol Box**

[figure not shown]

### 1.2 Principal research questions.

The primary aim of this study is to evaluate the effectiveness of aerosol box use, compared with no aerosol box use, for reducing HCP contamination during performance of AGMPs by a trained airway team during care of a simulated patients in respiratory failure due to COVID-19. We hypothesize that the use of an aerosol box, compared with no aerosol box use, will reduce HCP contamination caused by AGMPs during care of simulated patients in respiratory failure due to COVID-19.

The secondary aim is to determine if aerosol box use influences the time to successful completion and first-pass success rate for ETI and LMA insertion in trained airway teams. We hypothesize that there will be no significant differences in time to ETI and LMA insertion and first pass success rates when comparing airways teams using an aerosol box with teams not using an aerosol box.

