### **2.16, 2.17 *Statistical analysis.***

Demographic characteristics of participants including sex, profession, years of clinical experience and other identifiers (e.g. height, body surface area) will be reported using descriptive statistics between 2 study arms. For the primary outcome, assuming non-normal distribution of data, we will use Wilcoxon rank sum tests to compare the AOC in 3 different procedures in both airway providers and assistant roles. Analyses to evaluate the degree of contamination pre- and post-doffing of PPE will be conducted separately. Time to procedural completion and first pass success rates will be compared with the Wilcoxon rank sum tests.

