### **2.18 *Subgroup analysis.***

Although stratifying by sex during randomization will ensure equal distribution of different sex in both groups, the physical stature of each provider may be a factor that influences the extent of contamination. We will conduct secondary analysis to explore if factors other than aerosol box (i.e. sex, body surface area, number of years clinical experience of the airway expert, experience of doing multiple procedures within incubator) will influence the degree of contamination, time to successful intubation and LMA insertion, and first pass success rate for ETI and LMA insertion using mixed-effect linear regression model. The similar secondary analyses focusing on the degree of contamination of the airway assistant will be performed as well while stratified by these factors.

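### The secondary aim is met by a non-significant result: first-pass success and procedure time have no margin, no sample-size basis and only difference tests

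*Protocol*

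**What the plan says.** Protocol section 1.1 sets the question as one of harm: the study will "evaluate if using an aerosol box adversely affects time to completion and first pass success rates for ETI and LMA insertion". It says the results can be "balanced against the degree of HCP contamination to inform clinical practice and potential changes to institutional policy". The same section cites a manikin study of 12 anesthesiologists in which "aerosol box use was associated with longer intubation times and lower first-pass success rates", and notes that those participants had very brief training and no airway assistant.

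Section 1.2 gives the hypothesis: "We hypothesize that there will be no significant differences in time to ETI and LMA insertion and first pass success rates". Section 2.16 gives the analysis: "Time to procedural completion and first pass success rates will be compared with the Wilcoxon rank sum tests". Section 2.10 bases the sample size on the primary outcome: 30 teams per arm for Cohen's d = 0.65 with three repeated measures and an intra-cluster correlation of 0.7, plus 2 teams per arm for missing data. Neither 1.2, 2.10 nor 2.16 gives a margin, an expected first-pass rate or an expected procedure time.

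Section 2.18 is a separate exploratory analysis: "We will conduct secondary analysis to explore if factors other than aerosol box" matter. Its list of outcomes ends with "first pass success rate for ETI and LMA insertion using mixed-effect linear regression model".

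**The concern.** A difference test can support the statement that the arms differ. Failing to reject does not support the statement that they are alike, unless the interval for the difference is narrow enough to exclude a difference that matters. Here the hypothesis itself is worded as non-significance, so any p-value above 0.05 satisfies it, however wide the interval.

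The direction of error matters. The sponsor's own background cites a signal of harm, and the performance result is to be set against a contamination benefit when practice and policy are decided. If a real fall in first-pass success is more likely than not to come out non-significant, it enters that balance as no difference.

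**Working it through.** **1. The plan's own figure.** Inputs from section 2.10: d = 0.65, alpha 0.05 (two-sided assumed), power 0.80, three measures per team, rho = 0.7. The variance factor for the mean of three correlated measures is (1 + 2 × 0.7)/3 = 0.80.

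n per arm = 2 × (1.960 + 0.842)² / 0.65² × 0.80 = 29.7, so 30. Power at 30 is 0.804 by the normal approximation. The figure reproduces, but only for the three-scenario mean of the primary outcome. First-pass success is one yes/no value per team per procedure, and BVM ventilation contributes none.

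**2. Power for first-pass success.** Control rates and falls are assumed, because the protocol gives none. On 0/1 data the tie-corrected Wilcoxon statistic, without continuity correction, is

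z = (p1 − p2) / √[ p̄(1 − p̄) × N/(N − 1) × 2/n ], with N = 2n.

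Exact enumeration of the two binomials gives:

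| Control to box | Power, n = 30 | Power, n = 32 | Non-significant |
|---|---|---|---|
| 95% to 85% | 0.264 | 0.282 | 72–74% |
| 90% to 80% | 0.194 | 0.205 | 80–81% |
| 95% to 80% | 0.453 | 0.480 | 52–55% |
| 90% to 75% | 0.335 | 0.357 | 64–67% |
| 95% to 75% | 0.633 | 0.663 | 34–37% |
| 90% to 70% | 0.499 | 0.532 | 47–50% |

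At 30 per arm (normal approximation), 80% power needs a fall of about 28 points from 95% or 31 from 90%.

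**3. Combining ETI and LMA.** If rho = 0.7 also held here (assumed), the effective n is 30 × 2/1.7 = 35.3 per arm. Power is then 0.29 (95% to 85%) and 0.21 (90% to 80%). With full independence, n = 60, it is 0.45 and 0.33.

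**4. Time.** At 30 per arm (normal approximation), a 0.5 SD delay is detected with power 0.49. The detectable difference at 80% power is 2.802 × √(2/30) = 0.72 SD.

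**5. Precision.** The 95% CI half-width for the risk difference is 1.96 × √[2p(1 − p)/n]. At n = 30 this is 0.110 for p = 0.95, 0.152 for 0.90, 0.181 for 0.85 and 0.202 for 0.80. At n = 32 it runs from 0.107 (95%) to 0.196 (80%).

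**6. Illustration.** Suppose 27/30 succeed without the box and 23/30 with it, a fall of 13.3 points. Then z = 0.1333 / √(0.8333 × 0.1667 × 60/59 × 2/30) = 0.1333/0.0970 = 1.37, p about 0.17, and the stated hypothesis is met. The 95% CI is 13.3 ± 1.96 × √(0.9 × 0.1/30 + 0.767 × 0.233/30) = 13.3 ± 18.6, from a 5-point rise to a 32-point fall.

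**7. The model in section 2.18.** With 64 teams and two procedures there are 128 attempts. At 80% to 95% success (assumed), failures number 128 × 0.20 = 26 down to 128 × 0.05 = 6. A linear model with several covariates so near the ceiling can give fitted rates above 100%.

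**The case against.** The strongest reply is that nowhere does the protocol say a non-significant test will be read as safety. The aim in section 1.2 is neutrally worded, nothing in 2.16 forbids estimates and intervals, and an unseen SAP may supply them. This is partly right: a reader might infer a written rule that p > 0.05 means no harm, and no such rule exists. What remains is that the hypothesis is itself phrased as non-significance, the test is named, and no other criterion is given.

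The hypothesis is also a reasoned one. The cited study had little training and no assistant, and this trial provides both. That makes harm less likely, but does not make a non-significant test evidence against it.

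The sizes rest on assumed rates, and no figure in the protocol marks 10 or 15 points as important. That stands. Against a 20-point fall, power is between 0.50 and 0.66, so the fall would be missed in a third to a half of trials.

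Four further readings are tempting and unsupported:

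- That the linear model hides a box effect. It appears only in the exploratory analysis of other factors; small numbers and the missing margin cause the miss.
- That the Wilcoxon test is the fault. On yes/no data it nearly equals the uncorrected chi-square test: 28/30 against 22/30 gives p = 0.039 and 0.038.
- That non-normal contamination data contradict a linear model in 2.18. That model's assumption concerns residuals.
- That section 1.4 sets first-pass success against contamination. It names insertion times; the balancing statement is in 1.1.

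**Conclusion.** The concern holds in a limited form. The secondary hypothesis is a no-difference claim tested by difference tests, with no margin and no sample-size basis, on a question of harm meant to inform policy. At assumed control rates of 90% to 95% and 30 to 32 teams per arm, two-sided 0.05, falls of 10 points would be non-significant about 72% to 81% of the time, and falls of 15 points about 52% to 67%. Larger falls fare better: 20 points would be missed about 34% to 50% of the time. These percentages depend on the assumed rates; the missing criterion does not.

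A reader might want a single margin that the trial can support. The margin that could be excluded with 80% power when true rates are equal is 2.802 × √[2p(1 − p)/n], from about 15 points (95%, n = 32) to about 29 (80%, n = 30). No single value, such as the 21 points for 90% at n = 32, should be written in: a margin must come from clinical reasoning, not from the available n.

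The linear model for first-pass success is a separate, minor defect confined to an exploratory analysis.

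**What to change.** - **Sections 1.2 and 2.16.** Restate the secondary aim as estimation. Report the risk difference in first-pass success and the difference in procedure time, each with a 95% CI. Conclude no adverse effect only if the unfavourable limit excludes a margin that is clinically justified and fixed before data are seen; otherwise report the result as inconclusive.
- **Section 2.10.** State the expected precision as a range: a half-width of about 11 to 20 points for success of 95% down to 80%.
- **Section 2.18 (minor).** For first-pass success, replace the linear model with a logistic mixed or penalised logistic model with few covariates.

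The cost is wording; the estimation option needs no extra teams. The downside is that reassurance becomes harder to claim. If the sponsor wants a powered non-inferiority claim, a 10-point margin (one-sided 0.025, 80% power, equal true rates) would need about 75 teams per arm at 95% success or 142 at 90%, well beyond this trial.

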### 1.3 Why is a trial needed now?

The second wave of the COVID-19 pandemic is upon us. Now, more than ever, it is critically important to identify strategies to protect healthcare workers from infection with SARS-CoV-2. Failure to do so may result in workforce shortages, which in turn will compromise patient safety. AGMPs are procedures that have the potential to create aerosols, or tiny particles suspended in the air that can contain pathogens such as viruses. Studies conducted during the prior SARS-CoV epidemic suggest that AGMPs play an important role in virus transmission via aerosols. A systematic review identified BVM ventilation and ETI as AGMPs associated with highest risk of SARS-CoV transmission. As SARS-CoV and SARS-CoV-2 are from the same family of Coronaviridae, this data raises significant concern regarding the role of AGMPs in nosocomial

transmission of SARS-CoV-2. Given the paucity of experimental data on nosocomial virus transmission and AGMPs, most guidelines for infection control are based expert opinion. No studies to date have quantified the degree of HCP contamination resulting from AGMPs performed while caring for critically ill patients. Demonstrating reduced HCP contamination with use of the aerosol box during AGMPs can potentially enhance HCP safety, resulting in reduced workforce shortages due to illness.

#### ***1.4 How will the results of this trial be used?***

Research assessing strategies to mitigate HCP risks of contamination is critical to reduce rates of HCP infection with SARS-CoV-2. Our study will be the first to provide supportive evidence for aerosol box use with trained airway teams performing AGMPs in patients with respiratory failure. Our study will also be the first to provide a quantitative measure of HCP contamination patterns (pre- and post-doffing) in conjunction with ETI and LMA insertion times. In combination, these metrics provide key information that will inform clinical practice, institutional airway management policies, and PPE protocols. Data from our study will be used to inform future clinical studies on real COVID-19 patients, or in other clinical contexts where AGMPs pose a health risk to HCPs. Existing partnerships with institutions within the International Network for Simulation-based Pediatric Innovation, Research and Education (INSPIRE network) will enable rapid dissemination of aerosol box training material across all continents. Given that aerosol boxes are both pragmatic and affordable, positive results from our study will inform clinical practice changes that will help mitigate healthcare provider risks and reduce morbidity and mortality from SARS-CoV-2.

#### ***1.5 Risks to participants.***

There are no risks to the safety of participants involved in this trial.

## **2.0 THE PROPOSED TRIAL**

### ***2.1 Trial design.***

We plan to conduct a prospective, randomized controlled trial at four INSPIRE network sites (Alberta Children's Hospital, Ste. Justine Hospital, and Children's Hospital of Los Angeles and The Hospital for Sick Children). Simulation-based research confers the advantage of answering research questions without risk of harm to HCPs or patients, which is particularly important when studying a disease process with high mortality. Ethics approval has been submitted at all sites. Two participants will form an airway team, recruited to play the roles of airway provider and airway assistant for management of a simulated, critically ill COVID-19 patient. Participants will be randomized by team into either the control arm (i.e. no aerosol box) or the intervention arm (i.e. use of aerosol box) (Figure 2). Following randomization, all participants will view a short video orienting them to the simulated clinical environment. Intervention arm teams will view an additional video orienting them to the use of the aerosol box, and receive up to 15 minutes of hands-on training (see below for details). After orientation, teams will participate in three sequential simulation scenarios. The order of scenario delivery will be randomized to eliminate scenario order as a potential confounder. The location and nature of equipment, temperature and humidity within the resuscitation room will be standardized across all sites. A Laerdal Resusci-Anne manikin will be used as a simulated patient.

**Figure 2 – Study Design**

[figure not shown]

## 2.2 Trial interventions.

The aerosol box is a transparent, plastic cube covering the patient’s head and shoulders, with circular access ports on the front of the box allowing for access to manage the airway (see budget). An additional four access holes (i.e. two on either side of the box) allow for airway assistants to access the patient airway (Figure 3). As our study includes only one airway assistant, the two holes that are not in use will be sealed shut during the study. The airway assistant will be directed to stand in a standardized position, to the immediate right of the airway provider. In a prior study, an aerosol box placed over the head of an adult volunteer demonstrated air leaks out of the box during exhalation and coughing that could be eliminated with the addition of a plastic drape. For this reason, we have incorporated a plastic drape extending from the top of the box down to the patient’s chest to prevent spread of aerosols. In another experiment, the addition of continuous wall suction to the aerosol box setup resulted in significantly decreased airborne particle exposure (for the airway provider) compared to aerosol box use without suction. Given that wall suction is readily available and accessible in most acute care areas, our aerosol box setup will include wall suction, with suction tubing running into the aerosol box at one point along the bottom of the box near the head of the patient. Wall suction will be set at 200 mmHg, which is consistent with the pressure used in prior studies and measured in the engineering lab of [name] (co-applicant) to generate a negative airflow of approximately 50 L/min.

All participants (i.e. airway provider and airway assistant) randomized to the intervention arm will receive aerosol box training. A short video will orient them to the design of the aerosol box and include expert-modeled demonstration of strategies for optimal BVM ventilation, ETI, and LMA insertion using an aerosol box with a 2-person airway team. The training video will be shot in English and French to permit viewing across study sites in Alberta, Ontario and Quebec. After viewing the video, participants will work in pairs to practice all three procedures for a maximum of 15 minutes, providing them opportunity to coordinate their movements to optimize efficiency. After each procedure, they will receive feedback from a local airway and aerosol box expert (i.e. site investigator).

**Figure 3 – Aerosol Box Setup**

[figure not shown]

***Simulating Aerosolization.***

The amount of aerosolization that occurs in real patients is highly variable and dependent upon many factors (e.g. viral load, method of aerosolization, etc.), making it impossible to exactly replicate aerosolization of SARS-CoV-2 virus in the simulated environment. In our study, we aim to create a model of aerosolization by standardizing various aspects of care (e.g. ventilation pressures, particle size and volume deposited, lung compliance), thus allowing us to make comparisons between different contexts (ie. aerosol box vs no box; BVM vs. LMA vs. ETI). To visualize aerosolization of particles, we will adapt methodology successfully utilized by members of our research team in studies evaluating aerosolization during airway management. GloGerm™ (Glo Germ Company, Moab, UT, USA) is a nontoxic, invisible fluorescent resin marker that illuminates when exposed to ultraviolet (UV) light. The SARS-CoV-2 virus requires a water and mucus envelope to spread, with the size of these virus-containing envelopes varying from larger droplets ( $>60\ \mu\text{m}$ ) to smaller airborne particles or infectious droplet nuclei ( $5\text{-}10\ \mu\text{m}$  diameter). With a particle size of approximately  $1\text{-}5\ \mu\text{m}$ , Glo Germ™ represents a reasonable surrogate for aerosolized SARS-CoV-2. AGMPs can generate aerosols in two ways: by mechanically inducing and dispersing aerosols, or by inducing the patient to cough to produce aerosols. Our study focuses on aerosols mechanically induced by three commonly performed AGMPs: BVM ventilation, LMA insertion, and ETI. Glo Germ™ (0.5 mL) will be applied to the oropharynx and trachea of the manikin to simulate secretions. Glo Germ™ will be aerosolized from the mechanical pressures and airflow associated with bagging, or from manipulation of the airway, which is consistent with the current understanding of aerosolization mechanics in AGMPs. Participants will titrate ventilation pressures to 20 cm H2O peak inspiratory pressure, and 5-6 cm H2O peak end expiratory pressure using a digital pressure manometer that provides real-time feedback. Pilot work done by our research team using the methods (and ventilation pressures) described above resulted in contamination on the hands, torso, face shield, and feet of airway providers during BVM ventilation. This suggests these methods are sufficient to produce a measurable amount of Glo Germ™ particles during manual ventilation.
